## Methods/Design

### Study design

The current study uses a multicentre, cluster randomized, parallel-controlled superiority design with blinded assessment (a flow diagram of the study design is presented in Figure 
1). The course of this trial will comprise a 4-week intervention and a 12-week follow-up period. The control group will receive SLT and initial therapies, while, the experimental group will receive additional scalp acupuncture. There is a total of five time points, including baseline, 2 weeks after treatment, 4 weeks after treatment, 6 weeks after follow-up, and 12 weeks after follow-up. Fujian University of Traditional Chinese Medicine (FJTCM), as an undertaker of this project, is responsible for completing the training of the rehabilitation therapists in a unified standard way before the study, and supervising their operations regularly during the study at all clinical sites. The Center of Evidence-based Medicine in FJTCM, which plays a role in randomization and will be blinded to the intervention, is an independent department employed to monitor and analyze data. The present project, funded by the State Administration of Traditional Chinese Medicine, has received approval from the local ethics committees of every center (Fujian: 2013KY-006-01, approval received in July 2013; Henan: 2014HL010, approval received in March 2014; Shandong: 2013KY-006-01, approval received in March 2014) participated in the study. Written informed consent is required prior to participation from each participant or their guardian, and they will be informed of the nature of this trial including its purpose, procedures involved, expected duration, potential risks and discomfort, as well as the possible benefits they will receive from it. There is no time limit for them to ask related questions and respond to the invitation to participate. Participants will be also informed that they are free to withdraw from the study at any stage for any reason and their personal information will be undisclosed and kept securely at FJTCM.

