### Sample size

Referring to a trial
[23] with the same protocol as the present study, the effective rate of Broca’s aphasia after stroke was 64.71% in the control group (π_1_) and 85% in the experimental group (π_2_). Preliminary epidemiological findings show that there will not be less than 16 qualified participants recruited from each CHC. Prior data indicates that the intra-CHC correlation coefficient (ρ) is likely to be 0.030. Each group will consist of 132 individuals according to the formula:

(1)$$n=\frac{{\left(\mu_{\alpha }+\mu_{\beta }\right)}^{2}\;\left[\pi_{1}\;\left(1-\pi_{1}\right)+\pi_{2}\;\left(1-\pi_{2}\right)\right]\left[1+\left(m-1\right)\;\rho \right]}{{\left(\pi_{1}-\pi_{2}\right)}^{2}}$$

with a type I error of 5% (α = 0.05) and 90% power (β = 0.10). There will be 290 subjects included in total, allowing for a dropout rate of 10%.

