### Statistical methods

Statistical analysis in this study will be performed by a statistician who is not involved in this trial and works in the Center of Evidence-based Medicine in FJTCM. Analysis of all data will be conducted with SAS software (version 8.2, SAS Institute, Cary, North Carolina, United States), and two-sided *P* < 0.05 was considered statistically significant.

Descriptive statistics will be expressed in different forms according to the types of the data in each group. That is to say, continuous variables will use mean and standard deviation for normal distribution, with median and interquartile range for non-normal distribution, and categorical variables will use proportions with their standard error. Comparison of baseline characteristics, the primary or secondary outcomes between groups will use the *t*-test or Mann-Whitney test for continuous variables and Pearson chi-squared or Fisher’s exact test for categorical variables. Changes in effect sizes of primary or secondary outcomes from baseline to each time point for two groups will be expressed using the paired *t*-test or Wilcoxon signed-rank test.

The primary outcomes will be analyzed using full analysis set (FAS) and per protocol set (PPS), with the secondary outcomes using FAS. Analysis of the primary and secondary outcomes should be on the basis of the intention-to-treat (ITT) population. The safety set (SS) will be used to assess adverse events.

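### The article states an intention-to-treat basis but fixes visit-by-visit tests that, run on observed scores, leave dropouts out of the later between-group comparisons

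*Protocol article*

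**What the plan says.** The Statistical methods section of the protocol article fixes three things.

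- **Between-group comparison** of primary and secondary outcomes: t-test or Mann-Whitney for continuous variables, chi-squared or Fisher's exact for categorical ones.
- **Change from baseline** to each time point within each group: paired t-test or Wilcoxon signed-rank.
- **Populations**: "The primary outcomes will be analyzed using full analysis set (FAS) and per protocol set (PPS"), with the full analysis set for secondary outcomes, followed by "Analysis of the primary and secondary outcomes should be on the basis of the intention-to-treat (ITT) population".

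The Sample size section states "There will be 290 subjects included in total, allowing for a dropout rate of 10" percent. The Study design section tells participants that they are "free to withdraw from the study at any stage for any reason". Outcome measures and Table 1 schedule the language, daily-living and quality-of-life scores at baseline and at weeks 3, 5, 11 and 17. The article names no imputation, no repeated-measures model and no missing-data sensitivity analysis. It also does not say that patients without a score are excluded.

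**The concern.** An intention-to-treat basis means that every enrolled patient of a randomised CHC counts in the arm of that CHC. A two-sample test at week 17 can count only those who have a week-17 score. Unless a value is supplied for the others, the stated population and the named tests do not match at any visit where scores are missing.

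This matters more than usual here. Only one arm receives acupuncture, and the Discussion concedes that there is no placebo control and no double-blinding, so reasons for leaving may differ by arm. The Discussion also relies on the 12-week follow-up to judge whether improvement lasts, and that is where loss has had longest to accumulate. A patient who leaves after week 3 or week 5 has already given scores that say something about later status. Separate tests at weeks 11 and 17 do not use them.

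**Working it through.** **1. The plan's own figures.** Inputs from the Sample size section: effective rates 64.71% and 85%, at least 16 patients per CHC, intra-CHC correlation 0.030, 90% power, α = 0.05 (two-sided, from Statistical methods).

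- Design effect: 1 + (16 − 1) × 0.030 = 1.45.
- n = (1.960 + 1.282)² × [0.6471 × 0.3529 + 0.85 × 0.15] × 1.45 / (0.85 − 0.6471)² = 131.70, rounded up to 132 per group. This reproduces the plan.
- Total with allowance: 264 × 1.10 = 290.4, so 290. This also reproduces.

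**2. Who is left at the final visit.** 290 × 0.90 = 261, or 130.5 per arm against 132 required. About 29 patients have no final score. Those lost late still have scores at earlier visits, so the earlier sets may be larger than 261.

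**3. When the observed comparison is biased.** With dropout fraction d, true arm rate p and rate r among dropouts, those observed have rate c = (p − d·r)/(1 − d). The bias of the difference is d_E(c_E − r_E) − d_C(c_C − r_C), with E for experimental and C for control. It vanishes when the two products are equal.

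Illustration on the planning rates. The dropout splits and r (the same in both arms) are assumptions. Example: 15% experimental and 5% control dropout, r = 25%. Experimental (0.85 − 0.15 × 0.25)/0.85 = 0.9559; control (0.6471 − 0.05 × 0.25)/0.95 = 0.6680; difference 28.8 points.

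| Dropout, experimental / control | True difference | r = 0% | r = 25% | r = 50% |
|---|---|---|---|---|
| 10% / 10% | 20.3 | 22.5 | 22.5 | 22.5 |
| 15% / 5% | 20.3 | 31.9 | 28.8 | 25.7 |
| 5% / 15% | 20.3 | 13.3 | 16.4 | 19.5 |
| 10% / 10% | 0 | 0 | 0 | 0 |
| 15% / 5% | 0 | 8.0 | 4.9 | 1.8 |
| 5% / 15% | 0 | −8.0 | −4.9 | −1.8 |

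The 31.9 is an extreme corner: it requires every remaining experimental patient to respond.

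**4. On the score scale.** If dropouts are k SD worse than stayers in both arms, a 15%/5% split gives a bias of (0.15 − 0.05)k. If 10% leave each arm but only one arm loses poor performers, the bias is 0.10k. Both give 0.025, 0.05 and 0.10 SD for k = 0.25, 0.5 and 1. The standard error with 130.5 per arm is √(2/130.5) = 0.124 SD, or 0.149 SD after multiplying by √1.45 (taking the planning correlation to apply to the scores). The bias is then about 0.17 to 0.67 standard errors.

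**5. Simulation, as a check on order of size.** Assumptions: no true effect, 145 per arm, no clustering, adjacent-visit correlation 0.8 to 0.9, control dropout depending on the week-3 score (odds 2.7 to 4.5 times higher per SD worse), experimental dropout at random.

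- 10% dropout per arm: bias at week 17 about 0.04 to 0.09 SD; the nominal 5% test rejects in about 6.5% to 12% of trials.
- 15% control and 5% experimental: about 0.06 to 0.125 SD and 8% to 17%.

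In this setting poor performers leave control, so the bias runs against acupuncture. Using the baseline and week-3 scores brings the bias within 0.005 SD, but that is built in, because dropout was generated from the week-3 score.

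**The case against.** The strongest reply is that this is an unstated missing-data rule, and a condensed article may leave such rules to the full protocol or analysis plan. The named tests can be run on imputed data, the article nowhere says completers or observed cases, and a full analysis set is a usual way of putting intention-to-treat into practice. All of that stands. A reader might infer that the trial will report a completers-only analysis under an intention-to-treat label, or that naming both sets is itself an error. The document supports neither. Patients lost late also still count at the visits they attended.

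A reader might also take the simulated rejection rates as false claims of benefit for acupuncture. They are not: in that scenario the excess rejections favour control. The dropout mechanism is assumed and one-sided, and clustering is left out. With the design effect of 1.45 the standard error is about 1.20 times larger, so a bias of 0.4 to 0.75 standard errors becomes about 0.33 to 0.62. If dropout and its relation to outcome are alike in both arms, there is no bias under no effect. The weekly calls and at-least-monthly home visits in the Follow-up section may also keep loss low.

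The objection does not remove the point about method. The article fixes the between-group analysis as separate tests by visit. Even with a sensible population, those tests make no use of earlier scores from patients who later leave.

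**Conclusion.** The point holds in a limited form. The article pairs an intention-to-treat statement with tests that, on observed scores, give an available-case comparison at each visit: about 261 of 290 patients at the last one if the planned 10% dropout occurs. That comparison can be biased either way if dropout depends on outcome and differs by arm. Poor performers leaving the experimental arm favour acupuncture; poor performers leaving control count against it. The document does not determine the size. The figures of roughly 0.025 to 0.10 SD, or 2 to 8 percentage points under no true effect with a 15%/5% split, rest on assumed dropout patterns. The change is worth making because a better analysis is available from visits already scheduled.

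**What to change.** - **Continuous scores (CRRCAE, MBI, SF-36).** Replace the visit-by-visit between-group tests with one likelihood-based longitudinal mixed model: arm, visit, arm-by-visit, baseline score, correlation within patient and a CHC random effect. Use small-sample degrees of freedom, because at 16 or more patients each there are at most about 290/16 ≈ 18 CHCs. Read the week-5 and week-17 contrasts from this model.
- **BDAE-C severity grade (0 to 5).** Use an ordinal counterpart with the same structure, since this is one of the two primary outcomes.
- **Population.** Define the primary population as all enrolled patients of randomised CHCs. Keep those with only a baseline score, either by treating baseline as one of the responses or by multiple imputation that respects CHC.
- **Sensitivity.** Add one analysis that shifts the unobserved scores in one arm at a time.

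The cost is revised wording and slightly more programming, with no new visits or data. The model assumes that scores are missing at random given what was observed, and the sensitivity analysis probes this. If the statistical analysis plan already does this, only the article's text needs to be aligned with it.

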## Discussion

Nearly 20 to 25% of all stroke patients suffer from aphasia
[36], and approximately half of the initially affected patients still suffer from aphasia one year after stroke
[10,12]. Acupuncture, which proved to have a positive therapeutic effect on aphasia in acute stage stroke patients
[37], is considered as a good choice for chronic stroke patients with aphasia searching for complementary and alternative medicine as longterm treatment at a low cost.

We adopt a randomized, parallel-controlled, single-blind design in this trial to guarantee the quality level of the study. In consideration of the characteristics of stroke-induced aphasia, we will investigate the value-in-apply of combined SLT to scalp acupuncture treatment from the view of safety and efficacy, by the way of comparing the cost-effectiveness ratio of aphasia rehabilitation between CHCs and high-grade hospitals. We will also judge the longterm stability of improvements by a 12-week follow-up after intervention and dynamically observe the changes of curative effects by setting five assessment points (baseline, 2 and 4 weeks after intervention,6 and 12 weeks after follow-up).

A number of studies have come to an agreement that aphasia treatment is effective in enhancing recovery
[38-41]. However, there is a controversy about the role of the course of disease on outcomes. Some trials hold the view that further improvement of language abilities is very limited beyond 6 months after the onset of stroke
[42] and therapy provided immediately after stroke results in more beneficial effects than deferred treatment
[43].Others think that language abilities can be significantly improved in the chronic stage after a stroke when training is sufficiently intensive
[44-47]. In the present trial, if possible, we intend to make a stratified analysis according to the course of the disease to discover the best time to start treatment. In addition, cortical plasticity is recognized as the main mechanism of functional recovery basing on neuroimaging findings
[48-50]. In this study, we will use *f*MRI to observe the changes of activation of brain hemisphere structures attributed to the treatment.

A limitation of this study is that this protocol is not double-blind and has no placebo control. However, the intervention group will be blinded to the evidence-based medicine center to decrease possible bias. The study also cannot eliminate the confounding effects from the spontaneous recovery in the early stage of stroke.

If successful, this project will offer a low-cost appropriate technology for the CHCs and could be implemented on a large scale, both in China and worldwide. Scalp acupuncture therapy, which can be performed in a CHC instead of in a high-grade hospital, will relieve the stress of hospitalization and reduce the financial burden for the patient and healthcare system.

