### Inclusion criteria

The eligible participants should meet all the following criteria: (1) have been diagnosed with stroke according to the criteria regulated by the Fourth National Cerebral Vascular Disease Conference
[22], and confirmed as first stroke by a computed tomography (CT) or magnetic resonance imaging (MRI)examination; (2) be no more than two years post-stroke; (3) suffer from Broca’s aphasia after stroke, determined by the neurologist or rehabilitation physician and speech and language therapist, ascertained with Chinese Rehabilitation Research Center Standard Aphasia Examination (CRRCAE); (4) be between 18 and 80 years of age; (5) have provided written informed consent.

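### The planned stratified analysis by time since stroke cannot show the best time to start treatment; it can at most explore whether the added effect of acupuncture varies with time since stroke

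*Protocol article*

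**What the plan says.** In the Discussion, the authors note the dispute over whether aphasia therapy still helps late after stroke. They then state, on condition that it proves feasible, "we intend to make a stratified analysis according to the course of the disease to discover the best time to start treatment". No strata, cut-points or decision rule are given there.

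The other relevant statements are these:

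- **Inclusion criteria:** patients must "be no more than two years post-stroke". Time since stroke is therefore observed and not assigned.
- **Randomization and blinding:** the CHC is the unit allocated, to the experimental or the control group.
- **Sample size:** the calculation concerns one overall comparison of effective rates, "64.71% in the control group" and "85% in the experimental group".
- **Primary outcomes:** score differences are to be examined both between the two groups and within each group.
- **Statistical methods:** two-group tests and paired tests are named, and "two-sided *P* < 0.05 was considered statistically significant".
- **Discussion, limitations:** "The study also cannot eliminate the confounding effects from the spontaneous recovery in the early stage of stroke".
- **Baseline tests:** the duration of the stroke is already recorded.

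**The concern.** The best time to start treatment is a question about what would happen to the same patients if they began earlier or later. This trial assigns acupuncture or no acupuncture. It does not assign when treatment begins.

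Early and late entrants also differ by selection. The Discussion itself says that about half of those initially affected are still aphasic at one year, so a patient recruited late is by definition a persistent case. A difference between strata could reflect who is in them and not the timing of treatment.

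Within-group change adds a second problem. The Background says spontaneous recovery tends to level off by one year. Change from baseline would therefore tend to look larger in an early stratum even if acupuncture added nothing.

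What is at stake is a statement on timing that the data cannot carry, in a project whose stated goal is large-scale use in communities.

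**Working it through.** **1. The plan's own figure.** Inputs from Sample size: π₁ = 0.6471, π₂ = 0.85, difference 0.2029, ρ = 0.03, and m = 16 because "there will not be less than 16 qualified participants recruited from each CHC". Two-sided α = 0.05, power 90%.

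- Variance sum: 0.6471 × 0.3529 + 0.85 × 0.15 = 0.2284 + 0.1275 = 0.3559.
- Design effect: 1 + 15 × 0.03 = 1.45.
- n = (1.960 + 1.282)² × 0.3559 / 0.2029² × 1.45 = 90.83 × 1.45 = 131.7, so 132 per group. This agrees with the protocol.

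All of that information is assigned to one overall comparison.

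**2. What separate tests in strata would do.** The following are assumptions and are not in the document: two equal strata, the same true benefit (64.71% v 85%) in both, a separate two-sided 5% test in each, and significance in one stratum only read as the best time.

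With n per arm per stratum, SE = √(0.3559 × DE / n), power p = Φ(0.2029/SE − 1.96), and the chance that exactly one stratum is significant is 2p(1 − p). A stratum holding 8 of a CHC's 16 patients has a design effect of 1 + 7 × 0.03 = 1.21. The values 1.45 and 1.0 bound it.

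| Per group | Design effect | SE | Power per stratum | Exactly one significant |
|---|---|---|---|---|
| 132 | 1.45 | 0.0884 | 63% | 47% |
| 132 | 1.21 | 0.0808 | 71% | 41% |
| 132 | 1.0 | 0.0734 | 79% | 33% |
| 145 | 1.45 | 0.0844 | 67% | 44% |
| 145 | 1.21 | 0.0771 | 75% | 38% |
| 145 | 1.0 | 0.0701 | 82% | 29% |

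The product formula treats the strata as independent, although they share CHCs. A simulation with a shared CHC effect and 8 or 9 CHCs per arm gives 34% to 42% with a design-effect correction, and 29% to 33% with uncorrected tests of the kind Statistical methods names. Other splits give other values: a 25/75 split gives 47% to 58%.

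**3. What the right test could do.** Suppose all the benefit (0.2029) lies in one of two equal strata and none in the other. The interaction estimate is the difference of the two stratum effects.

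- With the variance of step 1 in both strata, SE = √2 × stratum SE. At 132 per group and design effect 1.45 this is 0.125, so power is Φ(0.2029/0.125 − 1.96) = 37%. At 145 per group and design effect 1.0, SE is 0.0991 and power 54%.
- If both arms of the no-benefit stratum sit at 64.71%, its variance sum is 2 × 0.2284 = 0.4567. At 132 per group and design effect 1.45, SE = √((0.3559 + 0.4567) × 1.45 / 66) = 0.1336 and power is 33%.

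The range is thus roughly 33% to 54%. With the step 1 variance, 90% power would need about 2.8 to 4.0 times the 132 per group.

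**4. Which results spontaneous recovery affects.** A between-arm contrast inside a stratum has concurrent controls from randomised CHCs, so natural recovery is expected in both arms. The within-group changes named in Primary outcomes and tested by paired tests have no such protection when compared across strata.

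**The case against.** The strongest reply is that this is one conditional sentence in the Discussion. It is absent from Outcome measures and Statistical methods, and strata, cut-points and test may be fixed in an analysis plan that is not shown. A stratified analysis could include a test of heterogeneity. All of this is fair: the missing detail is not a fault, and nothing commits the investigators to publish a recommendation on timing. But the condition governs whether the analysis is done and not what it is said to show, and no analysis plan can make start time randomised.

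Three stronger readings are tempting, and the document does not support them.

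- A reader might infer that the plan yields a false best time in about two of five trials. The protocol states no number of strata and no rule based on significance in one stratum. The figure also uses effective rates, while the primary outcomes are scores on the China Rehabilitation Research Center aphasia examination (CRRCAE) and severity grades on the Chinese Boston examination (BDAE-C), for which no standard deviation is given. A valid interaction test would hold the false-difference rate at the nominal 5%.
- A reader might infer that every result within a stratum is mixed with spontaneous recovery. That holds for within-group changes only.
- A reader might infer that the authors ignore spontaneous recovery. They disclose it as a limitation.

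**Conclusion.** The point stands as a mismatch between a stated aim and what the design can support. Time since stroke is not randomised, late entrants are selected for persistent aphasia, the sample size serves only the overall effect, and none of the named tests asks whether the effect differs between strata. That conclusion rests on the document alone.

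The 29% to 47% range is only an illustration of what can go wrong when significance is compared across strata. It depends on the assumptions in step 2 of the working and does not describe the CRRCAE or BDAE-C scores. The main comparison of acupuncture with control is not affected. The change is worth making because it is cheap and alters what the trial may conclude about timing.

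**What to change.** Restate the aim as exploring whether the added effect of acupuncture varies with time since stroke, and drop the claim to find the best time to start. Base it on a treatment-by-time-since-stroke interaction for the between-arm effect, using the stroke duration already collected and a model that respects CHC clustering. Report the estimate with its confidence interval as exploratory. State that no conclusion on timing will be drawn from stratum-specific p-values or from within-group changes.

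The cost is a change of wording, a weaker claim, and one additional cluster-aware model, since Statistical methods names none. Power for the interaction will be low, so a null result should not be read as evidence that timing does not matter.
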